## Abstract

**Introduction:** The immune checkpoint inhibitor (ICI) has been approved as the first-line therapy for metastatic gastric cancer in China. The treatment response of immune checkpoint inhibitor is highly dependent on the immune condition within the tumor microenvironment. Photodynamic therapy (PDT) has a long history in cancer treatment, and recent studies showed it had an immunomodulatory effect on the tumor. Here we will conduct a trial to assess whether or not a combination with Photodynamic therapy will improve the outcomes of immune checkpoint inhibitor-based treatment in patients with advanced or metastatic gastric cancer.

**Methods:** This study is a single-center, open-label, randomized controlled, phase 2–3 trial. Patients (18–65 years old) with untreated gastric or gastroesophageal junction adenocarcinoma will be eligible for this trial. Sixty participants will be enrolled and randomly divided into the test group (*n* = 30) and control group (*n* = 30) to receive photodynamic therapy in combination with immune checkpoint inhibitor plus chemotherapy and immune checkpoint inhibitor plus chemotherapy, respectively. The primary is progression-free survival (PFS). The secondary outcomes include objective response rates (ORRs) and the occurrence of adverse events. In addition, we will also assess the changes in peripheral blood mononuclear cells (PBMCs) and tumor microenvironment after photodynamic therapy treatment in the test group. Evaluation of the tumor response will be performed every two cycles for a maximum of eight cycles.

**Discussion:** Photodynamic therapy has an immunomodulatory effect on the tumor microenvironment; however, this has not been demonstrated for gastric cancer in a clinical trial. Based on our experience of photodynamic therapy treatment in digestive tract tumors, we plan to conduct a randomized controlled trial on this topic. This will be the first study to evaluate the synergistic effect of photodynamic therapy with immunochemotherapy for patients with advanced gastric cancer.

**Ethics and dissemination:** It was approved by the Institutional Research Ethics Committee of Lanzhou University Second Hospital (No. 2022A-491). When this trial is completed, it will be shared at conferences and submitted for a potential publication in a peer-reviewed journal.

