### 2.7 Outcomes

The primary outcomes are objective response rate (ORR) and progression-free survival (PFS). The best overall response from ICI plus chemotherapy initiation to disease progression or last follow-up will be used to analyze the ORR. ORR refers to the proportion of patients with complete response (CR) and partial response (PR). PFS is defined as the time from ICI plus chemotherapy initiation to the date of first documented tumor progression or death no matter which happens first. All evaluations of treatment response or progression will be conducted by experienced radiologists according to the RECIST 1.1 criteria (Eisenhauer et al., 1990). The safety will be assessed using the incidence of adverse events defined as any toxicity from intervention initiation to the study end according to the NCI-CTCAE 5.0 criteria (Institute, 2017). For patients who receive PDT treatment, a self-control assessment before and after PDT will be performed, in which the changes in peripheral blood mononuclear cells (PBMCs) and intratumoral gene expression profiles will be evaluated.

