### 2.11 Sample size estimation

We calculate the sample size based on the ORR. According to the published report, 48.6% of patients receiving ICI plus chemotherapy had an objective response (Shitara et al., 2020). Thus, we expected the ORR to be 50% in our control group. For the patients receiving PDT in combination with ICI plus chemotherapy, we assume that 85% of patients will obtain an objective response based on the experience from our center. Based on these expected proportions, we use a two-sided type I error of 5% with a power of 80% to determine the required lowest sample size. It is supposed that approximately 20% of patients may drop out of the trial. Considering all of these, a total of 60 patients (30 per group) are planned to enroll.

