### 2.13 Data analysis

All statistical analyses will be performed using the R software (version 4.0.2). The intention-to-treat and per-protocol approaches will be used for the analysis of the primary outcomes. The as-treated analysis will be used for safety analysis. Continuous data will be presented as mean with standard deviation or median with interquartile range. Categorical data will be presented as numbers with percentages. Student’s t-test or Mann-Whitney *U*-test will be used for the comparison of continuous data, while chi-squared test or Fisher’s test will be used for categorical data. For patients in the test group, the paired *t*-test or Wilcoxon signed-rank test will be used to analyze the difference in PBMC data before and after PDT treatment. The analysis of the gene expression profile will follow the standard procedure for transcriptomic analysis, and a protocol will be developed once the specimens are collected. The survival plot will be drawn for PFS using the Kaplan-Meier method. Log-rank test will be used to compare the difference between the two groups, and Cox regression analysis will be performed to estimate the hazard ratio with 95% CI. All statistical tests will be two-sided, and a significant level will be set at 5%.

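### The abstract makes PFS the sole primary outcome, section 2.7 makes ORR and PFS both primary, and the sample size rests on ORR alone, so the protocol does not fix which result decides success

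*Protocol article*

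**What the plan says.** Four places in the protocol article bear on the primary endpoint.

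- **Abstract:** "The primary is progression-free survival (PFS). The secondary outcomes include objective response rates (ORRs) and the occurrence of adverse events". PFS stands alone and ORR ranks with safety as secondary.
- **Section 2.7 (Outcomes):** "The primary outcomes are objective response rate (ORR) and progression-free survival (PFS"). Both are primary, with no ranking.
- **Section 2.11 (Sample size estimation):** "We calculate the sample size based on the ORR". The inputs are a control rate ("Thus, we expected the ORR to be 50% in our control group"), a test-group rate ("we assume that 85% of patients will obtain an objective response based on the experience from our center") and the error rates ("we use a two-sided type I error of 5% with a power of 80% to determine the required lowest sample size"). With a 20% dropout allowance the total is 60 patients, 30 per group. No hazard ratio, median or event number is given for PFS.
- **Section 2.13 (Data analysis):** "The intention-to-treat and per-protocol approaches will be used for the analysis of the primary outcomes", and "All statistical tests will be two-sided, and a significant level will be set at 5" per cent. PFS is compared by log-rank test with a Cox hazard ratio. Nothing says whether one or both primary outcomes must be significant.

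**The concern.** ORR is secondary in one place, joint primary in another and the sole basis of the sample size in a third. These statements cannot all hold. An analysis plan normally carries out the protocol's primary endpoint; here it would first have to choose between two versions of it.

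Suppose ORR is significant and PFS is not. Under the abstract the trial has failed. Under section 2.7 it has succeeded if either endpoint suffices, and failed if both are needed. The trial is open-label and described as phase 2–3, so the criterion for success should be unambiguous before outcomes are compared between groups.

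**Working it through.** **1. The plan's own figure.** Inputs from section 2.11: 50% versus 85%, two-sided 5%, power 80%. With the unpooled-variance formula, n per group = (1.960 + 0.842)² × (0.50×0.50 + 0.85×0.15) / 0.35² = 24.2, rounded up to 25. Then 25 × 1.2 = 30 per group, 60 in total. The stated number reproduces from the ORR inputs, so it is an ORR sample size.

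**2. Reading A: PFS alone is primary (abstract).** There is one primary endpoint, so no inflation, but the sample size was not derived for it.

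*Events needed for 80% power.* Schoenfeld, 1:1 allocation: events = 4 × (1.960 + 0.842)² / (ln HR)². The hazard ratios are assumptions, as the article gives none.

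| Assumed HR | Events for 80% power | Power if all 60 patients had an event |
|---|---|---|
| 0.5 | 66 | 77% |
| 0.6 | 121 | 51% |
| 0.7 | 247 | 28% |

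*Events likely to be seen.* Section 2.6 ends the study for a subject at up to eight cycles, section 2.5 gives three-week cycles, and section 2.9 adds an examination one month after the last dose: 8 × 3 + about 4 = 28 weeks, or about 6.44 months. I assume that PFS follow-up stops there, that event times are exponential and that nobody is lost. Expected events = 30 × (1 − e^(−λT)) + 30 × (1 − e^(−HR·λT)), with λ = ln 2 / control median. Power = Φ(√events / 2 × |ln HR| − 1.960).

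Example with control median 7 months and HR 0.6: λT = 0.099 × 6.44 = 0.638. Events = 14.1 + 9.5 = 23.7. Power = Φ(2.43 × 0.511 − 1.960) = Φ(−0.72) = 24%.

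Approximate power over the assumed range:

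| Control median | HR 0.4 | HR 0.5 | HR 0.6 | HR 0.7 |
|---|---|---|---|---|
| 5 months | 66% | 46% | 29% | 17% |
| 7 months | 55% | 37% | 24% | 14% |
| 9 months | 47% | 32% | 20% | 12% |

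**3. Reading B: both primary, either one suffices (section 2.7).** Each is tested at 5% (section 2.13). If independent, family-wise error = 1 − 0.95² = 9.75%; the upper bound is 10%. For positively correlated test statistics (bivariate normal, correlations assumed):

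| Correlation | Family-wise error |
|---|---|
| 0.3 | 9.5% |
| 0.5 | 9.1% |
| 0.7 | 8.3% |
| 0.9 | 7.0% |

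**4. Reading C: both primary, both required.** Each test at 5% keeps the error of the joint claim at or below 5%. The power of the joint claim is not addressed, and it cannot exceed the power for PFS in step 2.

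**The case against.** The sponsor can fairly say that the testing order, the lead analysis set and the multiplicity rule are commonly left to an analysis plan or full protocol that is not shown. That stands, and their absence from an article is not the point here. Condensing an article can drop detail, but it does not explain two incompatible statements of the primary endpoint.

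Four stronger readings are tempting, and the article does not support them.

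- *The error rate is near 10%.* This needs section 2.7's reading and a rule that either endpoint alone suffices. No section states such a rule. ORR and PFS both rest on RECIST assessment and are probably positively correlated, so even then the rate would probably be below 9.75%.
- *There are four primary tests, two endpoints in two analysis sets.* Reporting intention-to-treat and per-protocol results together is routine, and section 2.13 does not let the per-protocol result carry the claim.
- *The sponsor plans to choose after seeing the data.* The article says no such thing, and section 2.12 bars export and analysis of the data until the trial ends. The ambiguity makes a late choice possible, not planned.
- *PFS power is 24%.* That is one cell of a table of assumptions. Only the range can be quoted, though every cell lies below 80%.

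It is also fair to object that making ORR primary is a preference. The abstract chose PFS, and section 3 concedes the risk of bias from the open-label design. Keeping PFS, or both, with a stated rule would resolve the contradiction too.

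**Conclusion.** The contradiction stands: the abstract, section 2.7 and section 2.11 give three incompatible roles to ORR, and the article does not settle which result decides success. This should be corrected before outcomes are compared between groups.

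Its size depends on the reading. Under the abstract, the sole primary endpoint has no sample-size basis, and power is about 12% to 66% over hazard ratios of 0.7 to 0.4 and control medians of 9 to 5 months, with follow-up to about 28 weeks. All three inputs are assumptions, and longer follow-up would raise the figures. Under section 2.7 with either endpoint sufficient, the family-wise error is 9.75% if independent and about 7.0% to 9.5% for correlations of 0.9 to 0.3. If both are required, or PFS alone is primary, there is no inflation. The registry entry is not visible, so nothing is concluded about whether it agrees.

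**What to change.** State one primary endpoint, in the same words, in the abstract and section 2.7.

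The choice that matches the existing sample size is ORR in all randomised patients at two-sided 5%. PFS becomes the key secondary, tested at 5% only if ORR is significant, which holds the error across the two at 5% without more patients. The per-protocol analysis becomes supportive. The small downside is that PFS loses its stand-alone confirmatory claim.

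The wording change does not by itself secure 80% power for ORR in all randomised patients. By the pooled-variance formula, power is 84% with 30 per group and 75% with 24 (30 × 0.8). If every dropout counted as a non-responder, a worst-case assumption, the rates become 0.8 × 50% = 40% and 0.8 × 85% = 68%, and power with 30 per group is about 59%. The handling of patients without a response assessment should therefore be stated alongside.

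If the sponsor keeps PFS as primary, or keeps both, it should state the decision rule (PFS alone, either with a split of the 5%, a fixed order, or both required) and say in section 2.11 that the 80% power applies to ORR only. Powering PFS as well would need a re-derived sample size and an event target. Splitting the 5% equally would also cost ORR power: at 2.5%, the pooled formula needs 33 evaluable per group, and 33 / 0.8 rounds up to 42 per group, 84 in total.

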**Clinical Trial Registration:**
http://www.chictr.org.cn/, identifier ChiCTR2200064280.

## 1 Introduction

Gastric cancer, including gastroesophageal junction cancer, is one of the most common digestive tract malignancies. According to the 2020 Global Cancer Statistics report, there were 1,089,103 new cases of gastric cancer and 768,793 deaths worldwide in 2020 (Sung et al., 2021). As its dormant symptoms in an early phase, most patients have already suffered an advanced disease when they are diagnosed (Wagner et al., 2017). Patients with advanced or metastatic gastric cancer have a poor prognosis with a 5-year survival rate below 20% (Yang et al., 2020; Kahraman and Yalcin, 2021).

Immunotherapy with immune checkpoint inhibitors (ICIs) has achieved great success in cancer management due to its wide range of applications and good safety. In China, ICI plus chemotherapy has currently been recommended as first-line treatment for metastatic gastric cancer (Committee, 2022). However, the efficacy of ICIs is significantly dependent on the immune microenvironment with tumor tissues in each patient. In gastric cancer, patients with a high PD-L1 expression (CPS ≥ 5) could have superior benefits than those with low PD-L1 (CPS ≥ 1) (Janjigian et al., 2021). PD-L1 is thus used to select patients for ICIs treatment in clinical practice because it can reflect the immune microenvironment to some extent. However, most patients with gastric cancer have a poor immune condition that cannot meet the criterion of CPS ≥ 5 for ICIs usage. Thus, it will be of significance to find a measure to improve a patient’s tumor microenvironment and enhance the effects of ICIs.

Photodynamic therapy (PDT) is a local therapy for tumors, which has a history of almost 30 years (Dougherty, 1993). PDT uses a photosensitizer activated by light to kill cancer cells, which is achieved by the production of oxygen radicals. For gastric cancer, PDT is mainly used for early disease. It is not commonly used in advanced gastric cancer as its limited depth of irradiation. In recent years, an immunomodulatory effect of PDT was found in cancer conditions. PDT can induce a systematic immune response and lead to immunogenic cell death of the tumor cells (Beltrán Hernández et al., 2020). With the development of material science, a lot of novel drug delivery systems have been designed to achieve multifunctional combined therapies (Cheng et al., 2020; Fan et al., 2021; Chen et al., 2022; Cheng et al., 2022). Very recently, some studies have evaluated the feasibility of photoimmunotherapy by encapsulating photosensitizers and immunostimulatory drugs into one micelle and revealed a synergistic effect of these combined strategies in inducing the immunoresponsive tumor microenvironment (Chen et al., 2022; Cheng et al., 2022). This means PDT has the potential to help recruit immune cells into the tumor microenvironment and improve the effects of immunotherapy.

Here, we plan to perform a phase 2–3 open-label clinical trial by studying the outcomes of PDT in combination with ICI plus chemotherapy versus ICI plus chemotherapy, aimed to determine the clinical value of PDT as an adjuvant for improving ICIs-based treatment in advanced or metastatic gastric cancer and gastroesophageal junction cancer.

## 2 Methods and analysis

### 2.1 Study design

This study is a single-center, open-label, 1:1 randomized, phase 2–3 clinical study in which we will evaluate the efficacy and safety of PDT in combination with immunochemotherapy for untreated gastric cancer (Figure 1). Meanwhile, we will also collect the specimens of tumor tissue and blood before and after PDT treatment to explore the PDT-induced changes in the immune system and the tumor microenvironment in patients with gastric cancer.

**FIGURE 1 F1:**
[figure not shown]
Flowchart of the trial. PDT, photodynamic therapy; ICI, immune checkpoint inhibitor; PFS, progression-free survival; ORR, objective response rate; AEs, adverse events.

### 2.2 Study setting

The study will be conducted at the Cancer Center of Lanzhou University Second Hospital. It is expected to complete in 18 months once initiated.

### 2.3 Inclusion criteria

All patients who meet the following criteria will be enrolled: 1) 18–65 years old; 2) untreated gastric or gastroesophageal junction adenocarcinoma confirmed by histopathological examination; 3) advanced or metastatic stage; 4) ECOG score 0–2; 5) expected survival >6 months; 6) having at least one measurable lesion; 7) adequate bone marrow, kidney and liver function defined as neutrophil count ≥1.5 × 10^9^/L, platelet count ≥100 × 10^9^/L, creatinine ≤1.5 times the upper limit of normal (ULN), total bilirubin ≤1.5 times the ULN, and aspartate transaminase and alanine aminotransferase ≤5.0 times the ULN; 8) and providing signed informed consent.

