### 2.4 Exclusion criteria

Any participants will be excluded when they have one of the following conditions: 1) multiple primary tumors; 2) prior usage of immunomodulator drugs or any medicines having a direct impact on the immune system; 3) pregnancy or lactation for women; 4) history of allergy to the tested medications or light sensitiveness; 5) contraindication to gastroscopy; 6) comorbidities including autoimmune disease, severe cardiovascular disease, mental illness or severe neurosis, gastrointestinal bleeding and other severe diseases; 7) other inappropriate condition for inclusion determined by the researchers.

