### 2.6 Termination of the trial

All regimens will continue until confirmed disease progression, unacceptable toxicity, drop out, or the study end. The study end for a subject is defined as treatment up to eight cycles. After eight cycles, patients will continue the treatment or change a new scheme according to the judgment of the investigator.

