Our cancer center has rich experience in PDT treatment in digestive tract tumors, which will provide support to assure the subjects receiving a homogeneous treatment in this trial. We used ICI plus chemotherapy as the standard scheme, which is in accord with the beneficence principle in medical ethics. In addition, this gives a promise of enough interested patients for recruitment. In this trial, we will only include patients with age ≤65, and poor health conditions will be excluded. This is based on the consideration that elderly patients with poor conditions are easier to drop out due to their intolerance of the assigned treatments. Decreasing the ratio of drop-outs can avoid the negative influence caused by it on data analysis and increase the validity of our results.

There are also some limitations in this trial. Firstly, chemotherapy will be concurrently applied with ICI in the schemes of this trial. This means this trial can just identify the effects of PDT for ICI combined with chemotherapy. How these effects come and whether PDT can synergize with either of the ICI and chemotherapy or both of them will be hard to explain. In the future, we will conduct further studies to clarify these when the roles of PDT in the tumor microenvironment are more demonstrated. Secondly, this is an open-label study, and blinding will not be used during the study. The risk of bias caused by this will inevitably impact the results to some extent. Finally, the sample size is small. It may be difficult to perform subgroup analysis with these subjects.

This trial is the first study to explore the clinical significance of PDT in improving the outcomes of ICI plus chemotherapy in patients with advanced or metastatic gastric cancer. This paper provided an interpretation of its design and methodology. The results of this trial will help us know the roles of PDT in gastric cancer and may give a novel combined strategy for immunotherapy.

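### Criterion 3 admits advanced, non-metastatic disease with no condition on resectability, which is wider than the document's own support for its control regimen

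*Protocol article*

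**What the plan says.** Section 2.3 opens with "All patients who meet the following criteria will be enrolled". Criterion 2 asks for "untreated gastric or gastroesophageal junction adenocarcinoma confirmed by histopathological examination" and criterion 3 for "advanced or metastatic stage". *Advanced* is not defined anywhere in the article. Nothing in it mentions resectability, operability or surgery. The only exclusion in 2.4 that could reach an operable patient is the last, "other inappropriate condition for inclusion determined by the researchers".

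On the control regimen, the Introduction says "ICI plus chemotherapy has currently been recommended as first-line treatment for metastatic gastric cancer". The opening of the Abstract (on the checkpoint inhibitor) and the first paragraph of the Discussion (on the combination) make the same kind of statement, again for metastatic disease. Later the Discussion states, with no limit by stage, "We used ICI plus chemotherapy as the standard scheme, which is in accord with the beneficence principle in medical ethics".

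Section 2.6 says when treatment ends: "All regimens will continue until confirmed disease progression, unacceptable toxicity, drop out, or the study end". Section 2.7 defines ORR and PFS without mentioning surgery, and section 2.10 makes the trial open-label.

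**The concern.** The *or* in criterion 3 makes *advanced* a category beside *metastatic*. For patients in that extra category, the article offers no support for its statement that the control arm receives standard treatment. That statement carries the ethical argument for the design.

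The second issue is interpretability. If operable patients are among those enrolled, some may later have their tumour removed. Resection can take away measurable lesions and change the risk of progression. The decision would be taken by people who know the arm, and it may depend on how well the tumour has responded. The comparison of ORR and PFS would then partly reflect who had surgery. Disease extent is also likely to be prognostic, and with 60 patients the article itself expects subgroup analysis to be difficult, so a mixed population would be hard to separate afterwards.

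**Working it through.** The point concerns eligibility wording, so most of the check sets passages side by side.

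**1. Do the criteria let an operable patient through?** Take an untreated, non-metastatic, operable patient aged 18–65 with locally advanced adenocarcinoma, ECOG 0, a measurable lesion, normal laboratory values and signed consent.

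| Rule | Outcome for this patient |
|---|---|
| 2.3, criteria 1, 2, 4, 6, 7, 8 | met |
| 2.3, criterion 3 (stage) | met if *advanced* includes locally advanced disease; nothing in the text rules this out |
| 2.3, criterion 5 (expected survival over 6 months) | met; it is a floor, so a good prognosis passes |
| 2.4, exclusions 1–6 | none concerns operability |
| 2.4, exclusion 7 | discretionary; resectability is not named |

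**2. How does the article use *advanced*?** The Introduction sets it against the early phase of disease, and says photodynamic therapy is used mainly for early tumours and seldom for advanced ones. The contrast is with early disease, not with resectable disease. That leaves room for locally advanced, operable tumours.

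**3. What supports the control regimen?**

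| Place | Population named |
|---|---|
| Abstract, Introduction paragraph (approval of the checkpoint inhibitor) | metastatic |
| Section 1 (recommendation of the combination) | metastatic |
| Section 3, first paragraph (use of the combination) | metastatic |
| Section 3, standard-scheme statement | no limit by stage |
| Section 2.3, criterion 3 | advanced or metastatic |

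The first three rows do not cover the population in the last two.

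**4. Does the planned sample size depend on this?** Inputs from section 2.11: ORR 50% versus 85%, two-sided 5%, power 80%, dropout 20%. The unpooled normal formula gives

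n = (1.960 + 0.842)² × (0.50×0.50 + 0.85×0.15) / 0.35² = 7.849 × 0.3775 / 0.1225 = 24.2, rounded up to 25 per arm.

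Then 25 × 1.20 = 30 per arm, or 60 in total, which reproduces the plan. No input refers to stage, so rewording criterion 3 leaves N at 60.

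**5. How much could surgery matter?** The documents give neither the share of operable patients nor the share resected. As an illustration only, assume a fraction f of both arms is resected before any response is recorded, with 24 evaluable patients per arm (30 × 0.8). With a pooled-variance normal test,

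power = Φ{[√n·Δ − 1.96·√(2p̄(1−p̄))] / √(p₁(1−p₁) + p₂(1−p₂))}.

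At f = 0 this is 75%.

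| f (assumed) | Resected counted as non-responders | Resected lost on top of the dropout |
|---|---|---|
| 10% | 61% | 70% |
| 20% | 49% | 65% |
| 30% | 39% | 59% |

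For f = 20% in the first column, the rates are 0.50 × 0.8 = 0.40 and 0.85 × 0.8 = 0.68. Both f and the handling of resected patients are assumptions. The table shows sensitivity and does not predict what will happen in this trial.

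**The case against.** The strongest reply is that the article plainly has incurable disease in mind. The Introduction treats advanced and metastatic gastric cancer as one group with 5-year survival below 20%. Treatment runs to progression or toxicity for up to eight cycles, and PFS is a primary outcome, which does not resemble a perioperative design. There is one centre, so sites cannot differ in how they read the word. Exclusion 7 lets the researchers turn away unsuitable patients, and the full protocol may define stage. The stated aim also uses *advanced or metastatic*, so criterion 3 matches the aim.

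Much of this is fair. It supports saying that operable patients *could* be enrolled, not that they *would* be. It does not supply an operative rule: the survival figure is background, discretion sets no common standard, and the aim uses the same undefined word. The mismatch with the support given for the control regimen remains, and it is a disagreement between statements in the article rather than a detail left out.

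Two stronger readings should be resisted. A reader might infer from section 2.6 that a resected responder becomes a dropout or a censored PFS time, so that censoring is informative. The text does not say this. Section 2.6 governs the end of treatment, section 2.7 counts progression or death with no censoring at surgery, and section 2.13 commits to intention-to-treat analysis of the primary outcomes. Censoring rules may also sit in an analysis plan that is not shown. A reader might also treat a chance imbalance in disease extent between the arms as bias. It is not bias: the two-sided 5% test already allows for it, and the documents give no share of non-metastatic patients from which to compute it.

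**Conclusion.** The point holds in limited form. As written, criterion 3 is wider than the document's own basis for calling the control regimen standard, and it does not keep out operable patients. If such patients enter, later surgery chosen in an open-label setting could alter response and progression. That consequence is conditional: it rests on *advanced* being read to include locally advanced operable disease, on such patients being recruited, and on some being resected. The documents quantify none of these, so no size of bias or loss of power is claimed, and the illustrated power figures stand or fall with their assumptions. The sample size of 60 is unaffected. This should be corrected because the remedy is specific and cheap; it is not a fatal flaw in the design.

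**What to change.** Reconcile criterion 3 with the Abstract, the Introduction and both statements in the Discussion:

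- State in section 2.3 whether *advanced* means unresectable disease, and in section 2.4 whether a patient with planned curative resection is eligible. Require both to be judged and recorded before allocation. Restricting entry to unresectable or metastatic disease would match the rationale as it stands. If the wider population is intended, the article needs to support the control regimen for that population too.
- Record locally advanced versus metastatic status at screening, where tumour CT is already scheduled. Use it as an adjustment factor in the ORR analysis (for example, logistic regression with arm and disease extent) and in the Cox model for PFS.

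The cost is a short eligibility clarification, one case report form field and one extra model term. The downside is a slightly smaller recruitment pool. If *advanced* was always meant as unresectable, recruitment does not change.
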